**Fig. 1 Fig1:**
[figure not shown]
Schedule of enrollment, interventions and assessments

### Randomization procedures

Randomization will be conducted using computer-generated random numbers (Epidat® version 3.1). The allocation sequence will be prepared by a researcher with no involvement in the study by using a blocked randomization model. Allocation concealment will be ensured using 34 sequentially numbered opaque and sealed envelopes. After performing the baseline assessments the treating clinician will open the envelope and reveal each participant’s group allocation.

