### Recruitment procedures

Participants will be recruited from different outpatient private clinics and rehabilitation services of different hospitals of the region of Valencia (Spain). In addition, posters will be distributed in the community and advertisements in social media will be placed to increase the potential number of participants in the study. Physical therapists and primary care practitioners will be contacted and invited to recruit participants after providing them with brief information about the study. Involved practitioners will identifiy potentially suitable patients and, after providing them with information about the study, will invite them to contact the research team. Upon contact by potential participants, a researcher will explain the study and assess them for study eligilibily via telephone. If the potential participant remains interested in participating in the study, they will be invited to a baseline session. During that session, one researcher will provide to the patient an information leaflet, confirm eligibility, and obtain a signed consent form. Baseline outcome data will be collected during this session, following which the participant will be randomized.

Adherence to treatment will be enhanced by careful explanation of the time demands of participation and regular contact by a researcher who will send repeated reminders to participants by email and make telephone calls to ensure adherence to the time schedule including follow-up sessions.

The schedule of the enrollment, interventions and assessments is shown in Fig. 1.

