### Blinding

Participants will be blinded to both study hypothesis and group allocation. It will not be possible to blind the treating physical therapists who are responsable of performing the interventions. All the assessments will be conducted by researchers who will be blinded to group allocation. Statitistical analysis will be performed by a statistician blinded to the study aims.

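### The unblinded treating clinician opens sequential envelopes from a blocked list, which leaves concealment open to envelope handling and partial prediction of later allocations

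*Protocol article*

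**What the plan says.** All references are to the protocol article.

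- **Randomization procedures.** "The allocation sequence will be prepared by a researcher with no involvement in the study", and the list is made "by using a blocked randomization model". "Allocation concealment will be ensured using 34 sequentially numbered opaque and sealed envelopes". Then: "After performing the baseline assessments the treating clinician will open the envelope", which reveals the participant's group.
- **Blinding.** "It will not be possible to blind the treating physical therapists". On outcome measurement: "All the assessments will be conducted by researchers who will be blinded to group allocation".
- **Recruitment procedures.** "Physical therapists and primary care practitioners will be contacted and invited to recruit participants". These practitioners identify possible patients and ask them to contact the research team. A researcher screens by telephone. At the baseline session a researcher confirms eligibility and takes consent, baseline data are collected, and randomization follows.
- **Details of the interventions.** Trial therapists are mentioned in the plural, without a number. Those giving the CNS-focused program also meet for group discussions and quarterly case reviews.

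**The concern.** A sealed, numbered envelope hides the allocation of the patient in hand. It does not stop someone who knows the previous allocations from working out the next one when the list is balanced in blocks. The plan has the envelopes opened by the person who delivers the treatment, cannot be blinded and may prefer one arm. Two risks follow:

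1. **Handling.** The opener could open an envelope early or out of order.
2. **Prediction.** The opener knows at least some past allocations and can sometimes infer the next one.

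Either matters only if it changes who enters which arm. Physical therapists are a referral source, and the article does not say that referring and treating therapists are different people. At 17 per arm a few steered patients would count. As an illustration only (assumed, not from the plan), suppose three of 17 patients in one arm are each one SD (16 points) better on SPADI than they would otherwise have been. That arm's mean then moves by 3 × 16 / 17 = 2.8 points, about 17% of the 17-point target difference.

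The sentence on envelope opening can also be read as making the treating clinician the baseline assessor.

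**Working it through.** **Inputs from the article.** There are 34 envelopes, 17 per group (Sample size calculations; Randomization procedures). The list is blocked, and the opener is the unblinded treating clinician.

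**Not given, so varied here.** Block size (2, 4, 6) and number of clinicians sharing the envelopes (1, 2, 4). Further assumptions: 1:1 blocks of one fixed size known to the clinician, envelope numbers that show the position within the block, patients spread at random and equally over the clinicians, and no sharing of information.

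**The plan's own figure.** A two-sided t test (sidedness is assumed) with difference 17 and SD 16 has 80.2% power at 15 per group, which reproduces the 30 evaluable patients. Adding 15% gives 30 × 1.15 = 34.5, stated as 34. This is the number of envelopes.

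**Step 1: one clinician sees everything.** In a block of size 2m, an allocation is certain once all m places of one arm are used. The expected number of certain allocations per block is 2m/(m+1):

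- block 2: 2/2 = 1
- block 4: 4/3 = 1.33
- block 6: 6/4 = 1.5

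Over 34 envelopes:

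- block 2: 17 blocks × 1 = 17.0, and 17.0/34 = 50%
- block 4: 8 blocks × 1.333 = 10.7, with no certain allocation in the two left over; 10.7/34 = 31%
- block 6: 5 blocks × 1.5 = 7.5, plus 0.1 from the four left over (the fourth is certain only if the first three agree, probability 2 × 3/6 × 2/5 × 1/4 = 0.1); 7.6/34 = 22%

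**Step 2: several clinicians.** With K clinicians, an allocation is certain only if the clinician concerned saw all m places of the used-up arm, which has probability (1/K)^m.

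- K = 2: 17.0 × 1/2 = 8.5 (25%); 10.7 × 1/4 = 2.7 (8%); 7.6 × 1/8 = 0.95 (3%)
- K = 4: 17.0 × 1/4 = 4.25 (12.5%); 10.7 × 1/16 = 0.67 (2%); 7.6 × 1/64 = 0.12 (0.3%)

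Simulating 20,000 lists gave the same figures to within simulation error.

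**Step 3: best guess.** If the clinician always guesses the arm with more places left, the simulated share correct (chance is 50%) is shown beside the certain share:

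| Block size | Certain, K = 1 | Certain, K = 2 | Certain, K = 4 | Correct guess, K = 1 | Correct guess, K = 2 | Correct guess, K = 4 |
|---|---|---|---|---|---|---|
| 2 | 50% | 25% | 12.5% | 75% | 63% | 56% |
| 4 | 31% | 8% | 2% | 70% | 60% | 55% |
| 6 | 22% | 3% | 0.3% | 67% | 58% | 55% |

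**Step 4: who can act on a prediction.** Recruitment procedures gives screening, eligibility and consent to a researcher and puts randomization after baseline data. The treating clinician has no stated part in the decision to enrol. The routes left open are referral or its timing (if a treating therapist also refers), informal influence on the enrolling researcher, and the order in which envelopes are opened.

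**The case against.** The strongest defence is that prediction causes selection bias only when the predictor can influence entry, and the article gives entry to a researcher. Practitioners only identify patients and ask them to make contact. That stands, and it is the main reason why this is not a demonstrated failure. It does not cover a therapist who both treats and refers, because the article does not exclude that overlap.

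A reader might infer several stronger things that the document does not support:

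- **That one clinician sees every allocation.** Therapists are plural and several clinics and hospitals are involved, so the one-clinician column is a worst case. On the other side, case-review meetings make it unsafe to assume that nothing is shared.
- **That the block size must be 2.** Equal complete blocks that split 34 into 17 and 17 can only be of size 2 or 34. But sizes may be mixed (seven blocks of 4 and one of 6 also make 34), or the last block may be incomplete. Leaving the block size out of an article is not itself a fault.
- **That the article contradicts itself on baseline assessment.** The opening phrase of the envelope sentence is loosely attached. Read with Blinding and with the researcher-run baseline session, it is a wording problem.
- **That steering could never be detected.** Envelope numbers can be checked against enrolment order, and the analysis section plans a comparison of the groups for homogeneity. With 34 patients these checks are weak, but they exist.

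A last objection also stands: a therapist knows the arms of treated patients whoever opens the envelope. Moving the list elsewhere removes custody and out-of-order opening, but not that knowledge.

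**Conclusion.** The point holds as a vulnerability of moderate weight. The article itself chooses to have an unblinded, treating person open envelopes from a blocked list, and it states no protection against prediction. The share of allocations that would be certain in advance runs from 50% (one clinician, known fixed blocks of 2) to well under 1% (four clinicians, blocks of 6, nothing shared). The document does not show where in that range the trial lies. All these figures assume a fixed block size known to the clinician.

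It would be wrong to conclude that concealment has failed or that the SPADI comparison is biased. That would further require influence over referral, timing or envelope order, which the article neither describes nor rules out. Because the remedy is cheap and leaves the sample size unchanged, the change should be made.

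**What to change.** 1. **Release.** A person outside treatment, enrolment and assessment holds the list, for example the researcher who already prepares the sequence. That person releases each allocation to the therapist only after consent and the completed baseline data are logged. This removes envelope custody and out-of-order opening.
2. **Blocks.** Use randomly varied block sizes that are withheld from clinic and enrolling staff. This is the part that reduces prediction by a therapist who knows past allocations.
3. **Wording.** Reword the sentence in Randomization procedures so that blinded researchers do the baseline assessments, in line with Blinding, and so that the allocation is then released to the treating therapist.

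The cost is 34 releases at the present sample size, spread over the recruitment period. They would be made by a researcher who now has no continuing role, so that person must be available throughout. There would also be a short wait before the first session. The sample size and the analysis do not change.

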### Blinding

Participants will be blinded to both study hypothesis and group allocation. It will not be possible to blind the treating physical therapists who are responsable of performing the interventions. All the assessments will be conducted by researchers who will be blinded to group allocation. Statitistical analysis will be performed by a statistician blinded to the study aims.

### Statistical analysis including sample size calculation

#### Sample size calculations

The sample size will be calculated using G*Power 3.0.18 Software based on the SPADI as the primary outcome measure. To our knowledge, there are no studies investigating the effects of GMI or graded sensory discrimination training on FS. Based on similar studies applying physiotherapy on FS (SPADI mean of 66 points; standard deviation (SD) = 16) [8], and the minimal detectable change attained in the study by Tveita et al. (17 points) [41], to detect a 17-point (SD = 16) between-group difference, with 80% power and an alpha level of 0.05, a total sample size of 30 patients is estimated (15 per group). An allowance will be made for a 15% dropout rate, increasing the sample size to 34 patients (17 per group). However, since this calculation is not based in the use of GMI, to assure an adequate sample size, we will carry out a pilot study with 20 participants (10 per group) to test these assumptions. Mean differences and standard deviations from the inter-group comparison on the primary outcome (SPADI) will then be used to recalculate the sample size, if necessary.

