#### Statistical analysis

Data will be analyzed using the statistical package SPSS 21.00 for Windows. Statistical significance will be set at *p* < 0.05. Prior to statistical comparisons, all data will be tested for normal distribution. Then, a descriptive analysis of the data will be obtained for the dependent variables in the different assessment times. Subsequently, homogeneity of the two intervention groups will be studied. To confirm if there are differences in each group (intra-group comparisons), considering each group in isolation, between the four assessments in each of the variables (baseline, post treatment, 3-month follow-up, 6-month follow-up), repeated measures analysis of variance ANOVA will be used. To calculate inter-group differences between baseline and follow-ups, a four-way repeated-measures ANOVA will be conducted, with the scores of every primary and secondary outcome as dependent factors, with four levels corresponding to every time of assessment (t1, t2, t3 and t4), and the two intervention groups (CNS-focused treatment vs standard care treatment) as independent factors. Between- and within-group effect sizes for all quantitative variables will be measured with the Cohen *d* coefficient. An effect size greater than 0.8 will be considered large, around 0.5 moderate, and less than 0.2 small [42]. In cases of missing data, an intention-to-treat analysis will be performed. Double data entry will be carried out in order to promote data quality.

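### Thirty-four patients cover 4 losses (11.8%), not the stated 15% dropout; at 15%, about 29 complete and power is about 78–79% instead of 80%

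*Protocol article*

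**What the plan says.** All the figures are in the protocol article, mostly under Sample size calculations.

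- **Target:** the design aims "to detect a 17-point (SD = 16) between-group difference, with 80% power and an alpha level of 0.05". The SD comes from earlier physiotherapy work in frozen shoulder ("SPADI mean of 66 points; standard deviation (SD) = 16").
- **Evaluable size:** from these inputs "a total sample size of 30 patients is estimated (15 per group").
- **Dropout allowance:** "An allowance will be made for a 15% dropout rate, increasing the sample size to 34 patients (17 per group").
- **Operational size:** Randomization procedures carries the same number forward: "Allocation concealment will be ensured using 34 sequentially numbered opaque and sealed envelopes".
- **Possible revision:** a pilot of 20 participants is planned. Its SPADI mean differences and SDs "will then be used to recalculate the sample size, if necessary".

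**The concern.** A dropout allowance should leave the required number of patients after the assumed losses. Here the required number is 30 and the assumed loss is 15%, yet 85% of 34 is less than 30. The section therefore gives three figures (80% power, 15% dropout, 34 patients) that cannot all hold together.

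What is at stake is the accuracy of the main sample size statement. A reader would take it that the trial keeps 80% power with 15% of patients lost. There is almost no slack to absorb a shortfall, because 15 per group is the smallest equal group size that reaches 80%. The same inflation step could also be reused if the size is recalculated after the pilot.

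**Working it through.** **Inputs (protocol article, Sample size calculations).** Difference 17 points; SD 16; power 80%; alpha 0.05; 30 evaluable patients (15 per group); dropout 15%; 34 patients in total (17 per group).

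**Assumption.** The section does not say whether alpha is one- or two-sided. Two-sided is taken because it reproduces the stated 30; a one-sided t-test would need 12 per group, or 24.

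**Step 1: reproduce the 30.** The standardised difference is d = 17/16 = 1.0625. Power is that of a two-sample t-test, with n1 + n2 − 2 degrees of freedom and non-centrality d × √(n1·n2/(n1 + n2)).

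| Completers | Power |
|---|---|
| 14 + 14 | 77.2% |
| 14 + 15 | 78.7% |
| 15 + 15 | 80.2% |
| 17 + 17 (no loss) | 85.2% |

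Fifteen per group is the first equal size above 80%, so 30 is correct.

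**Step 2: apply the stated dropout to 34.**
- 34 × 0.85 = 28.9 expected completers, or 17 × 0.85 = 14.45 per group.
- The nearest whole-patient case is 5 of 34 lost (5/34 = 14.7%). This leaves 29, split 14 + 15, with power 78.7%.
- If each patient drops out independently with probability 0.15, power averaged over the possible losses in the two groups of 17 is 78.2%.
- Under the same independence assumption, the chance of ending with fewer than 30 completers is about 59% (1 − 0.408).

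**Step 3: the dropout that 34 does cover.** 34 − 30 = 4 losses, and 4/34 = 11.8%.

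**Step 4: the size that 15% requires.** 30/(1 − 0.15) = 35.3. Rounded up to equal groups this is 36 (18 per group), and 36 × 0.85 = 30.6 expected completers.

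**Step 5: where 34 probably comes from.** 30 × 1.15 = 34.5, which becomes 34 only if rounded down. Multiplying by 1.15 adds 15% of the evaluable number, whereas dropout is a share of those randomised. Even that shortcut, rounded up, gives 35, or 36 in equal groups.

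**The case against.** The strongest reply is that the gap is trivial: one completer, two recruited patients, about 1.5 power points. An SD of about 16.3 instead of 16 would cost the same, and the inputs are not known that closely. The figure of 34 is also not arbitrary, since it matches a common shortcut rounded down. All of this stands, and it limits the weight of the point. It does not make the sentence correct.

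The size is also provisional, because the pilot may lead to a new one. That step is conditional, however, and concerns mean differences and SDs. It says nothing about dropout, and 34 envelopes are already specified.

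The Statistical analysis section plans a repeated-measures ANOVA and promises intention-to-treat where data are missing. The powers above are therefore those of the sample size model, not of the planned analysis; the protocol's own 80% has the same limit. The intention-to-treat sentence does not rescue the allowance, because the protocol itself chose to inflate for dropout.

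Three stronger readings are tempting, and the document supports none of them:

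- **That power falls to 77% at 15% dropout.** That is the 14 + 14 case, which needs 6 of 34 lost (17.6%).
- **That the trial is materially underpowered or its validity is threatened.** The calculation shows only a small deficit against the stated target.
- **That adjusting for baseline SPADI would recover the loss.** Any gain depends on a baseline correlation that the document does not give.

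**Conclusion.** The point holds as a small arithmetic error. The 30 is right; the claim that 34 allows for 15% dropout is not. Thirty-four patients tolerate 4 losses (11.8%). At 15% dropout about 29 complete and power for 17 points is about 78–79%, against 80.2% with 30 completers. A true 15% allowance is 36 patients.

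This rests on the protocol's own difference, SD, power and alpha, on a two-sided t-test (the version that reproduces 30), and on dropouts contributing nothing to the comparison. The 78.2% and 59% figures also assume independent losses at exactly 15%. Under a cruder normal approximation 14 per group would suffice and the allowance would look adequate, but that approximation does not reproduce the protocol's 30.

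**What to change.** Replace the allowance sentence with one that the figures support, for example: *34 patients (17 per group) allow for 4 losses (11.8%); at 15% dropout the power to detect 17 points is about 78%.* This costs one sentence and no patients; the stated power at 15% dropout becomes slightly less favourable.

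If the sponsor prefers to keep both 15% and 80%, the size is 36 (18 per group). That means two more patients and a matching change to the envelope count under Randomization procedures.

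In either case, any recalculation after the pilot should divide the evaluable number by (1 − 0.15) and round up to equal groups. No gain from baseline adjustment should be claimed as making up the shortfall.

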### Data management

Data from the study will be only accessible to the research team and will be stored on password-protected computers at the University of Valencia. Paper-form data will be stored in locked cabinets located at the Department of Physiotherapy of that same university. In order to preserve data confidentiality study participants will be assigned an identification number which will be kept for the duration of the study. A list of participant identification numbers will be created and separated from the de-identified data. Statistical analyses will be performed keeping participant anonymity by using patient identification numbers and the statistician will be blinded to group allocation. Confidentiality will also be preserved when disseminating results by using group data.

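### The sample size is to be recalculated from the between-group SPADI difference seen in a 20-person pilot, an estimate too imprecise to secure the stated 80% power

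*Protocol article*

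**What the plan says.** The section on sample size calculations in the protocol article sets the trial up "to detect a 17-point (SD = 16) between-group difference", "with 80% power and an alpha level of 0.05". The SD comes from earlier physiotherapy work in frozen shoulder ("SPADI mean of 66 points; standard deviation (SD) = 16") and the 17 points from a published minimal detectable change. The result is 15 per group, raised for 15% dropout: "increasing the sample size to 34 patients (17 per group").

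Because these inputs do not come from trials of graded motor imagery, a pilot of 20 participants (10 per group) is added to test them. Then: "Mean differences and standard deviations from the inter-group comparison on the primary outcome (SPADI) will then be used to recalculate the sample size". The sentence ends by making this conditional on need. The section does not say what creates the need, whether the 17-point target survives, whether there is a minimum or maximum size, or whether the 20 enter the final analysis.

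Under randomization procedures: "Allocation concealment will be ensured using 34 sequentially numbered opaque and sealed envelopes". The statistical analysis section tests at p < 0.05 and describes no adjustment. Under data management, "the statistician will be blinded to group allocation".

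**The concern.** The rule names two inputs from the pilot: the SD and the observed difference between groups. The SD is a nuisance quantity, and updating it is ordinary practice. The difference is another matter. The 17 points state what the trial is designed to detect. If the pilot's observed difference takes that place, the target becomes an estimate from 10 patients per group.

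The stated purpose of the pilot is to make sure the trial is large enough. If the observed difference is too noisy to serve that purpose, the recalculated size may be far too small or needlessly large when nothing is wrong with the planning assumptions, and the 80% power no longer describes the trial that is run. If the pilot patients also enter the final comparison, a size chosen from their observed effect can raise the type I error of an ordinary test.

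**Working it through.** **Inputs.** All are from the section on sample size calculations: difference 17, SD 16, alpha 0.05, power 80%, 1:1 allocation, pilot of 10 per group. Sidedness is not stated. Two-sided is assumed because it reproduces the stated size; one-sided testing would need 12 per group.

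**1. The plan's own figure.** For a two-sample t-test, n per group ≈ 2(1.96 + 0.842)² / d² + 1 with d = 17/16 = 1.0625. This gives 15.70/1.129 + 1 = 14.9, so 15 per group. The exact noncentral t calculation agrees: power is 80.2% at 15 and 77.2% at 14. The stated 30 is reproduced. For dropout, 30 × 1.15 = 34.5 and 30/0.85 = 35.3; the stated 34 is close to both and is not at issue here.

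**2. Precision of the pilot difference.** SE = 16 × √(2/10) = 7.16 points. The 95% half-width on 18 degrees of freedom is 2.10 × 7.16 = 15.0 points.

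**3. Effect on the size.** Take a true difference of 17 and an SD of 16, and let the pilot land one SE either side:

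- Observed 17 − 7.16 = 9.84: n = 15.70/(9.84/16)² + 1 = 42.5, so 43 per group.
- Observed 17 + 7.16 = 24.16: n = 15.70/(24.16/16)² + 1 = 7.9, so 8 per group.

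Simulating one million pilots with difference 17 and SD 16, and recalculating to 80% power from the observed difference and SD:

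| Recalculated n per group | Observed difference and SD | 17 points fixed, SD only |
|---|---|---|
| Median | 15 | 15 |
| Quartiles | 9 and 29 | 12 and 18 |
| 5th to 95th percentile | about 5 to 145 | 9 to 24 |
| 2.5th to 97.5th percentile | 5 to 374 | 8 to 26 |

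Using the observed difference, the size is below the correct 15 in 48% of pilots, above 34 per group in 20%, and between 12 and 18 in only 23%.

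**4. Separate pilot.** If the main trial is then run at the recalculated size without the pilot patients, its true power is below 80% in 48% of cases and below 60% in 26%. Its type I error stays at 5%.

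**5. Pilot patients kept.** The size cannot then fall below the 10 per group already enrolled. The article gives no floor or cap, so those below are assumptions. Two million simulated trials with no true effect, with all patients in one unadjusted two-sided 5% t-test, gave:

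| Assumed rule | Type I error |
|---|---|
| Fixed at 15 per group | 5.0% |
| To 80% power, floor 10, cap 1000 | 8.2% |
| To 80% power, floor 10, cap 50 | 7.3% |
| To 80% power, floor 10, cap 30 | 6.7% |
| Increase only, floor 15, cap 1000 | 7.7% |
| Increase only, floor 15, cap 50 | 6.8% |
| Increase only, floor 17, cap 34 | 6.1% |
| Floor 17, cap 34, back to 17 if more than 34 needed | 4.7% |
| Floor 10, back to 15 if more than 50 needed | 5.0% |
| Within-group SD only, increase only | 5.1% to 5.2% |
| Within-group SD only, decrease allowed | 5.7% |

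**The case against.** The strongest reply is that the recalculation is conditional and protective. It occurs only if needed, its aim is an adequate size, and the text never says that 34 may be cut. That stands as far as it goes. A reader might infer that a favourable pilot will shrink the trial, but the article does not say so. What the reply does not remove is the named input. With no trigger or floor stated, and the observed difference feeding the formula, the low and the high results are both open; an increase-only reading would still let noise set how large the increase is.

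A reader might also infer that the 5% level fails whatever is done with the pilot. The documents do not support this. The article calls it a pilot study, which can be read as separate, and then alpha is untouched. The 34 envelopes equal the planned total and make no separate provision for 20 pilot patients, which makes retention plausible but does not establish it. Even with retention, the inflation depends on the resizing rule, and some rules give none. For the same reason, 5 per group and an inflated alpha belong to different readings and cannot occur together.

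Two further inferences are tempting. One is that an interim comparison by group contradicts the statistician's blinding. Groups coded A and B largely answer this, although the size of the difference would still be seen. The other is that 34 envelopes rule out a larger trial. The blocked sequence can be extended, so this is a matter of preparation.

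Finally, a journal article may leave floors, caps and the use of pilot data to the full protocol. That is fair for those details, but the choice of the observed difference as an input is stated in the article itself.

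**Conclusion.** The point holds for size and power. On the protocol's own SD and pilot size, the difference that would drive the recalculation has a standard error of 7.2 points against a 17-point target. With all assumptions true, the resulting size has a median of 15 per group and a 5th to 95th percentile range of about 5 to 145. The step does not do what it is there for. This part rests only on SD 16, 10 per group, approximate normality and complete pilot follow-up.

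The type I error part is conditional. It needs retention of the 20 in an unadjusted p < 0.05 test, and direct recalculation to 80% power. It is then about 6% to 8%. These figures come from a simple t-test on SPADI, whereas the plan is a repeated-measures ANOVA, so they indicate the order of magnitude. With a separate pilot there is no inflation.

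**What to change.** In the section on sample size calculations:

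- Remove the mean difference from the recalculation rule and keep 17 points as the fixed target.
- Re-estimate only the SD, preferably pooled over all 20 and blinded to group.
- Allow only an increase over 34.
- State whether the 20 count towards the trial.

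Under randomization procedures, provide for extending the blocked sequence and the envelopes if the size rises.

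The cost is a few sentences and, if needed, more envelopes. The statistical cost is that a blinded pooled SD absorbs part of any true effect. At 17 points it is about √(16² + 17²/4) = 18.1 instead of 16. Then n = 15.70/(17/18.1)² + 1 = 18.8, so 19 per group instead of 15, or 38 instead of 30 before dropout. A within-group SD avoids this but needs group-coded data at the pilot stage.
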